##### Power Consideration

We will aim to recruit at least 108 patients into the Medly Program at the HF clinic before analyses of patient-level outcomes are undertaken. This number is based on being able to detect a small effect size (Cohen *d*=0.3) in the number of hospitalizations because of HF within the first 6 months of enrollment with 80% power and an alpha of .05 (two-sided) [40]. This number considers that approximately 20% of patients will be “lost to follow-up,” which includes patient mortality and those who withdraw from the program before the 6-month time point. We anticipate recruiting this number in the first 18 months of the program.

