**Methods:**

The evaluation will use a mixed-methods approach. The quantitative component will include a pragmatic pre- and posttest study design for the impact and cost analyses, which will make use of clinical data and questionnaires administered to at least 108 patients at baseline and 6 months. Furthermore, outcome data will be collected at 1, 12, and 24 months to explore the longitudinal impact of the program. In addition, quantitative data related to implementation outcomes and patient usage patterns of the telemonitoring system will be reported. The qualitative component involves an embedded single case study design to identify the contextual factors that influenced the implementation. The implementation evaluation will be completed using semistructured interviews with clinicians, and other program staff at baseline, 4 months, and 12 months after the program start date. Interviews conducted with patients will be triangulated with usage data to explain usage patterns and adherence to the system.

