#### Patients

Patients can be enrolled into the Medly Program provided they (1) are 18 years or older, (2) have been diagnosed with HF and are followed by a cardiologist at the HF clinic, (3) can speak and read English (or have an informal caregiver who does) to adequately understand the text prompts in the Medly app, and (4) are able to comply with using Medly (eg, able to stand on the weight scale, able to answer symptom questions). As the Medly program is being implemented as part of the standard of care, there is no explicit exclusion criteria for participating in the program and its evaluation. The duration of program participation will be decided by patients and their treating cardiologist on an individual basis.

Upon enrollment into the Medly Program, patients will be presented with the option of answering questionnaires and participating in interviews related to the program evaluation. Patients will be asked to sign a written consent form before participating in the evaluation.

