### Data Collection and Analysis

#### Objective 1: Measuring the Impact of the Medly Program

##### Impact Indicators

The primary outcome for evaluating the impact of the Medly Program is the number of hospitalizations because of HF in the 6 months before versus the 6 months after enrollment. Secondary impact outcomes comparing 6-month to baseline values are described below.

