##### Planned Analyses

The primary analyses will be paired Student *t* tests and Wilcoxon signed rank tests comparing baseline and 6-month values for all patient-level outcomes. For patients enrolled in the Medly Program on hospital discharge, the 30-day readmission rate will be compared with the readmission rate before the launch of the Medly Program, as determined using hospital administrative data. Secondary analyses aimed at determining the longitudinal impact of the Medly Program (ie, using outcome data from the additional time points), and the correlation of independent variables (eg, patient characteristics and adherence rates) with outcomes will be analyzed using general linear mixed model procedures. In addition, descriptive statistics will be produced for all variables collected, which may inform necessary subgroup analyses. All statistical analyses will be performed using the statistical software application SPSS (IBM Corporation, USA) [39].

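### The recruitment target of 108 does not deliver 80% power after the stated 20% loss: about 86 pairs and 78.5% power remain, and the Abstract treats 108 as the number assessed at 6 months (minor)

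*Protocol article*

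**What the plan says.** The protocol article, Power Consideration, sets the target: "We will aim to recruit at least 108 patients into the Medly Program at the HF clinic before analyses of patient-level outcomes are undertaken". The basis is "being able to detect a small effect size (Cohen *d*=0.3) in the number of hospitalizations because of HF" within the first 6 months, "with 80% power and an alpha of .05 (two-sided"). On attrition it says: "This number considers that approximately 20% of patients will be" lost to follow-up, a category that covers deaths and withdrawals before 6 months. So 108 is a number at entry, before losses.

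The comparison is within patients. Impact Indicators defines the primary outcome as "the number of hospitalizations because of HF in the 6 months before versus the 6 months after enrollment", and Planned Analyses under Objective 1 gives the tests: "The primary analyses will be paired Student *t* tests and Wilcoxon signed rank tests comparing baseline and 6-month values for all patient-level outcomes".

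The Methods paragraph of the Abstract uses the same figure differently, describing "clinical data and questionnaires administered to at least 108 patients at baseline and 6 months". The Results section reports 166 patients enrolled as of April 4, 2018, with the primary impact analysis expected by January 2019.

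**The concern.** The section gives every input needed to recompute the sample size, and the result does not agree with them. If 20% of 108 patients are lost, too few pairs remain for the stated power. The match between 108 and 90 x 1.2 points to a familiar slip: to keep n patients after a fraction L is lost, one must recruit n/(1 - L), whereas n x (1 + L) is always smaller.

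The Abstract adds a second inconsistency that does not depend on how 108 was derived. A reader of the Abstract expects 108 patients with data at both time points; a reader of Power Consideration expects about 86. Both cannot follow from the same assumptions.

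At stake is whether the stated power and the number that triggers the analysis can be taken at face value.

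**Working it through.** **Inputs.** d = 0.3, power 80%, two-sided alpha .05, loss about 20% and target 108, all from Power Consideration; paired t test from Planned Analyses; one group measured before and after enrollment from Impact Indicators. I take d as the mean of the paired differences divided by their standard deviation. The article does not say so, but this reading leads to its figure.

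**Pairs needed.** For n pairs, power is the probability that a noncentral t variable with n - 1 degrees of freedom and noncentrality 0.3 x sqrt(n) falls outside the central t critical values at two-sided .05.

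- 89 pairs: 79.9%
- 90 pairs: 80.4%

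So 90 complete pairs are needed.

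**Reproducing the plan's figure.** 90 x (1 + 0.20) = 108.0, an exact match.

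**Inflation that preserves 90 pairs.** 90/(1 - 0.20) = 112.5, so 113. The difference from 108 is 5 recruits.

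**What 108 delivers.**

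- 108 x 0.80 = 86.4 pairs
- Power at 86 pairs: 78.5%; at 87 pairs: 79.0%
- d detectable with 80% power at 86 pairs: 0.306, against 0.30
- Largest loss at which 108 still keeps 90 pairs: 1 - 90/108 = 16.7%

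**Other routes to 108.**

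- Normal approximation: ((1.960 + 0.842)/0.3)^2 = 87.2 pairs. Rounded down, 87/0.8 = 108.75, so 109; rounded up, 88/0.8 = 110. At 86 pairs this approximation gives 79.4% power.
- One-sided t test: 71 pairs, too few to lead to 108; the section says two-sided in any case.
- Wilcoxon signed rank test with normally distributed differences (relative efficiency 3/pi = 0.955): 90/0.955 = 94.2, so 95 pairs. Then 95 x 1.2 = 114 and 95/0.8 = 118.75, so 119. Neither gives 108.

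Of these routes, only 90 x 1.2 gives 108 exactly. Correct inflation comes within 2 patients of it by the normal approximation but does not reach it.

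**The Abstract against Power Consideration.** If 108 patients had data at both time points, power at d = 0.3 would be 87.1%. Under the article's own loss assumption, 86 pairs give 78.5%.

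**The case against.** The strongest reply is that the gap lies within the precision of the assumptions. The loss is only approximate, the target is a minimum, and at 16.7% loss the 108 patients do keep 90 pairs. Enrollment has also passed the target: if all 166 patients contributed and 20% were lost, about 132 pairs would remain (166 x 0.8 = 132.8), with roughly 93% power. This stands, and it is why the point is minor. It does not make the stated inputs and the stated result agree.

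A second reply is that the article gives neither the figure 90 nor an inflation formula, so the slip is inferred. This also stands. The exact match makes it the likeliest route, but correct division with the normal approximation gives 109 to 110. The shortfall does not depend on the cause.

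A third reply is that the Abstract is a condensed sentence and Power Consideration supplies the loss assumption. That makes the wording an editorial matter, but the two statements still conflict.

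A reader might go further in three ways that the article does not support.

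- **Consent.** One might infer that optional consent shrinks the sample below 86, because "Patients will be asked to sign a written consent form before participating in the evaluation". The powered outcome, however, is HF hospitalizations. The Overview of the Study Design describes utilization as standard-of-care data from chart review, and Data Acquisition under Objective 1 takes it from the hospital record, with questionnaires used for verification. Whether consent limits that source is unclear, so erosion of the primary comparison is not shown.
- **The word small.** One might infer that it promises a small fall in admissions. The section attaches it to a standardized effect size, and objecting to the label is a matter of preference.
- **Admissions.** One might translate d = 0.3 into a percentage fall in admissions. That needs a baseline rate and a variance that the article does not give.

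**Conclusion.** Wrong as written, but minor. With d = 0.3 as a standardized paired difference, two-sided alpha .05, a paired t test and 20% loss, 108 recruits give about 86 pairs and 78.5% power, against the 90 pairs needed for 80%. The shortfall is about 4 pairs, 5 recruits and 1.5 power points. That 20% was added rather than divided out is a likely explanation, not an established one. The Abstract's use of 108 for both time points conflicts with 108 being the number before loss.

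A reader might infer that the study is materially underpowered. The article does not support that: the detectable effect moves only from 0.30 to 0.306, and enrollment stood at 166 by April 2018.

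**What to change.** In Power Consideration, state that 90 complete pairs are required and how they were inflated for loss. Then either restate the target as 113 (90/0.8), or keep 108 and report about 78.5% power at 20% loss.

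In the Methods paragraph of the Abstract, separate the number recruited from the number expected at 6 months: 108 and about 86, or 113 and about 90.

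The cost is a few sentences of text. No further recruitment is likely to be needed: 113 is 68% of the 166 patients already enrolled (113/166 = 0.68). The article does not report how many of them take part in the evaluation.

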###### Mortality and Prediction of Survival

Patient mortality will be tracked. In addition, the Seattle Heart Failure Model (SHFM) will be calculated at program entry. Projected SHFM survival versus actual survival will be compared [33]. The calculation of this score requires data on age, gender, New York Heart Association classification, weight, LVEF, systolic blood pressure, list of medications (including diuretics), laboratory results (hemoglobin, lymphocytes, uric acid, total cholesterol, and sodium), and QRS interval.

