##### Data Acquisition

Data collection will occur at baseline, 1 month, 6 months, 12 months, and 24 months, or until the patient exits the program. Data collected in addition to the primary evaluation period (baseline to 6 months) will provide an opportunity for post-hoc analyses aimed at quality improvement, including recommended duration of use. For example, the 1-month time point was included to determine if the bulk of changes to self-care and QoL occur immediately after enrollment. Similarly, longitudinal data will help determine whether patient-level impacts are sustained or change when using the system long term.

Health service utilization, laboratory results, mortality, prediction of survival, and select demographic information will be obtained from the hospital EMR. In addition, health service utilization information will be verified by patient participants through self-reports via a questionnaire.

Baseline and follow-up questionnaires containing the validated survey tools listed in Table 1 will be distributed to patients during regularly scheduled visits. Upon study enrollment, patients will be asked whether they prefer to be mailed the questionnaire or completing it using an online survey tool (SurveyMonkey [38]) in the event that they do not have a clinic visit scheduled for the data collection time point. In these situations, the questionnaires will be sent to the patient according to the preferred format and they will be given 2 weeks to respond, after which a member of the evaluation team will call the patient to remind them to complete the questionnaire.

**Table 1 table1:** Timing of outcome assessments for the impact evaluation.

Domain and measure		Baseline	1 month	6 months	12 months	24 months	Exit

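### The paired primary comparison gives no stated role to patients who die or leave the program before 6 months, and is liable to favour the program if leaving tends to follow an HF admission

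*Protocol article*

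**What the plan says.** All references are to the protocol article.

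- **Impact Indicators:** the primary outcome is "the number of hospitalizations because of HF in the 6 months before versus the 6 months after enrollment".
- **Planned Analyses (Objective 1):** the primary analyses are paired *t* tests and "Wilcoxon signed rank tests comparing baseline and 6-month values for all patient-level outcomes". The section gives no analysis set and no rule for a patient without a full 6-month period.
- **Power Consideration:** the recruitment target of at least 108 allows for about 20% lost to follow-up, "which includes patient mortality and those who withdraw from the program before the 6-month time point".
- **Data Acquisition (Objective 1):** "Data collection will occur at baseline, 1 month, 6 months, 12 months, and 24 months, or until the patient exits the program". Utilization and mortality come from the hospital electronic medical record (EMR), and patients verify utilization by questionnaire.
- **Table 1:** number of hospitalizations is marked at baseline, 6, 12 and 24 months, and Exit.
- **Patients:** "The duration of program participation will be decided by patients and their treating cardiologist on an individual basis". Leaving before 6 months is therefore possible by design.
- **Mortality and Prediction of Survival:** mortality is tracked, and "Projected SHFM survival versus actual survival will be compared".
- **Limitations:** there is no distinct comparator group.

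**The concern.** Leaving a telemonitoring program is not the same as leaving the hospital's records, and death is an outcome of heart failure rather than a gap in the data. The plan puts both under loss to follow-up. Its primary test needs a before value and a 6-month value, so the natural reading is that the contrast is made among patients who survived and stayed.

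If patients tend to die or withdraw after an HF admission, that group has been selected for having few post-enrolment admissions. Its pre-enrolment counts are not selected in the same way. The result is an apparent fall in admissions even if the program does nothing. With no comparator group, no control arm shares and offsets the attrition. The same 6-month contrast is used for days in hospital and for the cost comparison, so the effect would carry over to them.

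**Working it through.** **1. The plan's own figure.** Inputs from Power Consideration: d = 0.3, 80% power, two-sided alpha 0.05, 20% loss. With a paired *t* test (noncentral *t*), 89 pairs give power 0.799 and 90 pairs give 0.804, so 90 pairs are needed. 90 × 1.2 = 108, the stated target. (The normal approximation gives 88 pairs, and 88/0.8 = 110, close to the same.) So the 20% are budgeted to yield no pair. If exactly 20% are lost, 108 × 0.8 ≈ 86 pairs remain, with power 78.5%. The sample size is not the problem; selection is.

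**2. Exit triggered by an admission.** Assumptions, none from the documents: HF admissions are Poisson with mean λ = 0.35 per 6 months both before and after (no effect), and each post-enrolment admission leads to death or withdrawal before month 6 with probability q.

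- Completers' post mean = E[N(1−q)^N] / E[(1−q)^N] = λ(1−q). Their pre mean stays λ, so the false reduction equals q.
- Share leaving = 1 − exp(−λq).
- The false-benefit rate comes from simulating 108 enrollees with a paired *t* test in completers (10,000 runs; nominal 2.5% in the favourable direction).

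| q | False reduction | Share leaving | False-benefit rate |
|---|---|---|---|
| 0.1 | 10% | 3.4% | 6% |
| 0.2 | 20% | 6.8% | 13% |
| 0.3 | 30% | 10.0% | 25% |
| 0.5 | 50% | 16.1% | 62% |

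Every share leaving is below the plan's 20%. Shared frailty, where sicker patients have more admissions in both periods, does not remove this. Given frailty f, completers average λf before and λf(1−q) after, so the ratio is still 1−q. With gamma frailty of shape 1 or 0.5, the false-benefit rate is 22% to 24% at q = 0.3 and 49% to 55% at q = 0.5.

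**3. A fixed 20% leaving.** Suppose the whole cohort has no change and leavers have k times the completers' post rate but the same pre rate. Completers' post/pre ratio = 1/(0.8 + 0.2k).

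- k = 1.5: 1/1.1, a 9% false fall.
- k = 2: 1/1.2, a 17% fall; false-benefit rate 12% to 19% for assumed means of 0.5 to 1.0 admissions.
- k = 3: 1/1.4, a 29% fall; false-benefit rate 29% to 51%.
- k = 3 after and 1.5 before: 1.1/1.4, a 21% fall; false-benefit rate 17% to 28%.
- k = 3 in both periods: 1.4/1.4, no bias.

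**4. Stable patients also leave.** Return to step 2 and let a share s of admission-free patients leave as well. The completers' post/pre ratio = (1−q)e^(−λq) / (e^(−λq) − s·e^(−λ)).

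- q = 0.2, s = 0.20: 0.7459/0.7915 = 0.942, a 6% false fall with 21% leaving.
- q = 0.1, s = 0.23: 0.8690/0.8035 = 1.082, an 8% apparent increase with 20% leaving.

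**5. If the Exit counts were paired.** Under the step 2 model, suppose each leaver's count runs up to and includes the admission that triggers exit. The expected post count over λ is (1 − e^(−λq))/(λq) without frailty and 1/(1 + λq) with gamma frailty of shape 1.

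- q = 0.2: falls of 3% and 7%.
- q = 0.3: falls of 5% and 10%.
- q = 0.5: falls of 8% and 15%.

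Most of the bias goes. What remains arises because the post period is cut short without adjustment for time at risk.

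**The case against.** The strongest reply is that exclusion is inferred. Power Consideration sets a recruitment allowance, Planned Analyses names tests, and no sentence says that leavers are dropped. A condensed article may leave that rule to a fuller document. This stands as a limit on certainty. However, the article itself classes death and withdrawal as loss, ends data collection at exit and names the paired comparison as primary, and its sample size reproduces only if leavers give no pair.

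A reader might infer three stronger things that the documents do not support.

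- **That the admissions of leavers are discarded, or cannot be used in a paired test.** Table 1 collects hospitalizations at Exit, and a before count with an exit count does form a pair. What is missing is a stated role for that count and an allowance for its shorter period.
- **That the result is biased towards benefit.** The direction depends on why patients leave. Duration is set individually, and Table 2 separates patient-initiated from physician-initiated dropouts, so stable or disengaged patients may leave too. Steps 3 and 4 show the bias can shrink, vanish or reverse.
- **That actual survival in the Seattle Heart Failure Model (SHFM) comparison is overstated.** The article says mortality is tracked and gives no stop at exit for it. Survival would be overstated only if leavers were counted as survivors or their censoring were informative, and neither is stated.

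It is also fair that EMR look-up after exit loses the self-report check. That could leave the post period less completely ascertained than the pre period, an error that also favours the program.

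**Conclusion.** The concern holds in conditional form. As written, the plan treats death and program withdrawal before 6 months as loss, and gives their admissions no stated place in the primary analysis. If leaving tends to follow a post-enrolment HF admission, the completers' contrast is liable to favour the program. With 0.35 admissions per 6 months and no true effect, the false reduction is about 10% to 50% for q from 0.1 to 0.5, with a false-benefit rate of about 6% to 62% against a nominal 2.5%. Pairing the Exit counts would reduce the false fall to roughly 3% to 15% for q from 0.2 to 0.5.

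These sizes rest on assumed rates and an assumed exit mechanism, because the documents give neither. The point does not depend on the exact size: the mechanism is plausible in heart failure, nothing in an uncontrolled design offsets it, and the data needed to avoid most of it are largely in the hospital record.

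**What to change.** 1. Define the primary analysis set as all consenting enrollees, whether or not still in the program at 6 months.
2. Count HF admissions and deaths from the hospital EMR to month 6 or death, regardless of program exit. Distinguish leaving the program from withdrawing consent to the evaluation.
3. Compare post with pre as a rate that accounts for days at risk, for example a Poisson or negative binomial model with a log-days offset and patient-clustered robust standard errors. Raw counts for patients who die would not be enough, because death shortens the period and lowers the count.
4. Report deaths beside the rate ratio, with a sensitivity analysis counting each death as an event. Keep the completer paired test as a further sensitivity analysis.
5. State that vital status for the SHFM comparison is followed to a fixed date irrespective of program exit.

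**Cost:** a change of wording and continued record look-up after exit, to the extent that the consent covers it. The article expects the primary analysis by January 2019, and the look-up can be done from existing records. The drawback is that admissions at other hospitals after exit may be missed once self-report verification stops. An EMR-only count in both periods would check whether this matters.

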#### Objective 2: Implementation Evaluation

The mixed-methods implementation evaluation will be guided by the framework by Proctor et al, which describes outcomes that can serve as indicators of implementation success [41], and the Consolidated Framework for Implementation Research (CFIR). The CFIR describes factors influencing implementation success according to 5 domains: (1) intervention characteristics, (2) outer setting, (3) inner setting, (4) characteristics of individuals, and (5) process [42].

**Table 2 table2:** Implementation outcome indicators.

Implementation outcome	Definitions^a^	Indicator
Adoption	The intention, initial decision, or action to try or employ an innovation or evidence-based practice. Adoption may also be referred to as “uptake”	Number of clinicians having decided to use Medly to monitor patients
Implementation cost	The cost impact of the implementation effort	See objective 4 for cost outcomes associated with implementation of the Medly Program
Feasibility	The extent to which a new treatment, or an innovation, can be successfully used or carried out within a given agency or setting	Number of patients enrolled; rate of patient enrollment; number of patient-initiated dropouts from the program; number of physician-initiated dropouts from the program—or no uptake
Fidelity	The degree to which an intervention was implemented as it was prescribed in the original protocol or as it was intended by the program developers	Number and nature of calls or emails made to the telehealth analyst; proportion of the number of—alerts acknowledged over the total number of alerts, phone calls to patients over the total number of alerts triggered, and false or inappropriate alerts over the total alerts triggered
Penetration	The integration of a practice within a service setting and its subsystems	Percentage of clinicians using Medly over the total number of potential clinician users in the HF clinic

^a^Definitions are based on the definitions provided by Proctor et al [41].

